## Abstract

**Background:**

The incidence of non-AIDS defining cancer (NADC) is higher in people living with HIV (PLWH) than in the general population, and it is already one of the leading causes of death in the HIV-infected population. It is estimated that the situation will be aggravated by the progressive aging of PLWH. Early diagnosis through intensive cancer screening may improve the ability for therapeutic interventions and could be critical in reducing mortality, but it might also increase expenditure and harms associated with adverse events. The aim of this study is to evaluate an enhanced screening program for early diagnosis of cancer in PLWH compared to standard practice. The specific objectives are (1) to compare the frequency of cancer diagnosed at an early stage, (2) to analyze safety of the enhanced program: adverse events and unnecessary interventions, (3) to analyze the cost-utility of the program, and (4) to estimate the overall and site-specific incidence of NADC in PLWH.

**Methods:**

We will conduct a multicenter, non-blinded, randomized, controlled trial, comparing two parallel arms: conventional vs enhanced screening. Data will be recorded in an electronic data collection notebook. Conventional intervention group will follow the standard of care screening in the participating centers, according to the European AIDS Clinical Society recommendations, and the enhanced intervention group will follow an expanded screening aimed to early detection of lung, liver, anal, cervical, breast, prostate, colorectal, and skin cancer. The trial will be conducted within the framework of the Spanish AIDS Research Network Cohort (CoRIS).

**Discussion:**

The trial will evaluate the efficacy, safety, and efficiency of an enhanced screening program for the early diagnosis of cancer in HIV patients compared to standard of care practice. The information provided will be relevant since there are currently no studies on expanded cancer screening strategies in patients with HIV, and available data estimating cost effectiveness or cost-utility of such as programs are scarce. An enhanced program for NADC screening in patients with HIV could lead to early diagnosis and improve the prognosis of these patients, with an acceptable rate of unnecessary interventions, but it is critical to demonstrate that the benefits clearly outweigh the harms, before the strategy could be implemented.

**Trial registration:**

ClinicalTrials.gov NCT04735445. Registered on 25 June 2019

## Administrative information

Note: the numbers in curly brackets in this protocol refer to SPIRIT checklist item numbers. The order of the items has been modified to group similar items (see http://www.equator-network.org/reporting-guidelines/spirit-2013-statement-defining-standard-protocol-items-for-clinical-trials/).

## Introduction

### Background and rationale {6a}

Non-AIDS-defining cancer (NADC) is an important cause of morbidity and mortality in people living with the human immunodeficiency virus (PLWH), being currently one of the most frequent causes of death [1–5]. The incidence of cancer in PLWH is 2–3 times higher than in the general population [6–8]. A systematic review, analyzing data from more than 600,000 PLWH and 10,891 new cases of cancer, confirmed that the incidence of NADC has progressively increased since the introduction of combined antiretroviral therapy (ART), probably reflecting better viral-immune control and aging associated with increase in overall survival of patients living with the virus [9].

The most frequent types of NADC in PLWH are lung cancer, hepatocellular carcinoma, anal carcinoma and cervical carcinoma, although some studies have suggested that there could also be a higher incidence and/or severity of other malignant tumors, such as breast, prostate, colorectal, or skin cancer, including melanomas [10, 11]. In the era of ART, lung cancer has become the most frequent and deadliest cause of NADC in PLWH [12, 13], and greater lethality has been documented in PLWH than in the general population [14]. It is estimated that at least 1 in 3 PLWH will die due to malignant neoplasms in the coming years [15, 16]. The causes of this increased incidence of NADC are not well known and there are several factors that could play a role, including immunosuppression, chronic inflammation and immune activation, ART exposure, higher rates of coinfection with oncogenic viruses, and traditional cancer risk factors such as smoking [17, 18].

Despite the progressive aging of PLWH and the increase in the incidence of cancer, there is currently no consensus on the optimal screening strategy of cancer in this population. Some of the clinical practice guidelines of PLWH, such as the Spanish Gesida [18] or the European AIDS Clinical Society [19], recommend the screening approaches that have shown benefit in the general population in terms of mortality or greater probability of therapeutic success. However, these benefits have not been confirmed in PLWH, in which these strategies could be insufficient. Moreover, in the general population, there are currently no established recommendations for the screening in two of the neoplasms of special concern in HIV-infected patients, i.e., lung and anal cancer. For this reason, it is necessary to generate scientific evidence that informs clinical practice guidelines on the best screening approach in PLWH.

We hypothesize that a specific enhanced screening strategy for NADC in PLWH could favor the early detection of malignancies, improving the ability for therapeutic interventions, and thus reduce morbidity and mortality for cancer in PLWH, with an acceptable rate of unnecessary investigations, and may be cost-effective. To address this hypothesis, we have designed a clinical trial, in which patients are randomized to one of two strategies: enhanced screening versus standard of care practice. This trial aims to determine if the benefits of the enhanced screening outweighs the harms and if it is cost-effective.

Relevant studies informing on the main NADC in PLWH and examining potential benefits and harms of screening interventions are described next. For lung cancer, a standardized incidence rate 2.5 times higher in PLWH than in the general population, after adjusting for smoking, has been reported [20]. Smoking remains the main risk factor associated with lung oncogenesis, also in PLWH. The National Lung Screening Trial (NLST), a randomized study in the general population with more than 53,000 participants, demonstrated a 20% reduction in lung cancer mortality and a 6.7% reduction in overall mortality in those undergoing lung cancer screening with 3 annual low-dose computed tomography (LDCT) compared to simple chest x-ray [21].

In Spain, 92% of cases of hepatocellular carcinoma (HCC) in PLWH occur in patients coinfected with hepatitis C virus (HCV) [22], and its incidence seems to be increasing [23]. It has been suggested that HCC could be more symptomatic and be diagnosed in more advanced stages in PLWH [24]. As screening strategy, semiannual ultrasound is recommended in patients with cirrhosis of any cause, including cases of sustained viral response (SVR) to HCV antiviral therapy but with established chronic liver disease [18], and in patients co-infected with hepatitis B virus (HBV) regardless of the stage of fibrosis [19].

The incidence of anal cancer in the group of men who have sex with men (MSM) reaches 144 cases/100,000 people-year, and reported risk factors, in addition to MSM, include infection with oncogenic human papillomavirus (HPV), smoking, and immunosuppression. The incidence of this cancer increased significantly with the availability of effective ART at the end of the 1990s and the increase in survival of PLWH and is much higher than in the HIV-negative population [25]. Preventive measures and screening programs in PLWH based on anal cytology and anoscopy are advocated by some experts [26] but evidence of benefit remains unknown.

For cervical cancer, traditional screening programs based on Papanicolaou smear or liquid based cervical cytology have demonstrated to reduce cervical cancer mortality and might be enhanced by HPV genotype testing [19]. HPV genotype may aid at determining the periodicity of cytology, so that if high-risk genotypes (HPV-HR) are detected, a semiannual cytology could be recommended. However, this strategy has neither been evaluated in PLWH.

Finally, although controversy remains on whether PLWH have a higher risk for breast, prostate, colon, and skin cancer, these neoplasms have been included in the trial.

### Hypothesis and objectives {7}

Hypothesis: an enhanced program for screening of NADC in PLWH can lead to early diagnosis of cancer and improve the prognosis, with an acceptable rate of unnecessary interventions and being cost-effective.

General objectives: to evaluate the efficacy, safety, and efficiency of an expanded screening program for early diagnosis of cancer in patients with HIV compared to usual practice, within the framework of the Spanish AIDS Research Network Cohort (CoRIS).

Specific objectives: (1) to compare the frequency of cancer diagnosed at an early stage of disease with extended screening versus usual practice, (2) to analyze safety of the program: adverse events and unnecessary interventions, (3) to analyze the cost-utility of the extended screening program, and (4) to estimate the overall and site-specific incidence of NADC in PLWH.

### Trial design {8}

This protocol has been designed as a multicenter, randomized, parallel-group, and superiority trial.

## Methods: participants, interventions, and outcomes

### Study setting {9}

The study will be carried in the framework of the Spanish network of AIDS research (CoRIS), including 30 centers, being all of them Spanish academic hospitals.

### Eligibility criteria {10}

Inclusion and exclusion criteria for participants:

Inclusion criteria: adult patients ≥ 18 years with confirmed HIV infection and who agree to participate in the study and sign the informed consent.

Exclusion criteria: any active AIDS-defining disease, current or past NADC, life expectancy < 5 years, pregnancy or lactation, patients who refuse to participate in the study, any other criteria that in the judgment of the clinician should prevent the patient to participate in the study.

Eligibility criteria for study centers: Spanish hospitals with HIV/AIDS Unit and Infectious Diseases/HIV (ID/HIV) specialists.

Eligibility criteria for study individuals who will perform the interventions: ID/HIV specialists, radiologists, gynecologists, and surgeons.

### Who will take informed consent? {26a}

Participants meeting the study criteria will be invited by their doctors in charge to join the study during their routine medical visits, regardless of time from HIV diagnosis and the standard screening procedures being carried out in their centers, explaining the possible benefits and risks of the trial, and they will obtain the informed consent to participate in the study.

### Additional consent provisions for collection and use of participant data and biological specimens {26b}

An additional consent will be provided for collection and use of participant biological specimens that will be stored in a biobank.

## Interventions

### Explanation for the choice of comparators {6b}

The trial will compare the frequency of NADC diagnosed at an early stage in patients undergoing an enhanced screening program compared with those following conventional standard of care screening according to the European AIDS Clinical Society recommendations.

### Intervention description {11a}

Conventional group:

a. Semi-annual ultrasound and alpha-fetoprotein for all patients with cirrhosis and those with HBV infection with any degree of fibrosis.

b. Digital rectal examination and anal cytology every 1–3 years for all MSM men and anoscopy in case of cytology abnormal.

c. Cervical cytology every 1–3 years to all sexually active women, at least in those between 25 and 64 years.

d. Mammogram every 1–3 years to women between 50 and 70 years.

e. Rectal digital exam ± prostate-specific antigen (PSA) every 1–3 years for all men> 50 years.

f. Fecal occult blood test every 1–3 years in people between 50 and 75 years.

Enhanced group:

a. Annual LDCT to patients over 40 years of age, active smokers or who have quit in the last 3 years, with an accumulated index ≥ 20 pack-years and without contraindications for thoracic surgery, and without lung infections in the last 2 months.

b. Semi-annual ultrasound and alpha-fetoprotein for all people with chronic liver disease with fibrosis ≥ F3 of any cause (including HCV infection) or with any fibrosis for patients with HBV. Serum will be collected from all participants to be able to subsequently perform additional determinations such as alpha-fetoprotein-L3, decarboxyproprombin, or alpha-L-fucosidase.

c. Semi-annual digital examination and anal cytology to all MSM men and anoscopy in case of abnormal cytology.

d. Semiannual cervical cytology to all sexually active women between the ages of 21 and 64, including cotest (cervical cytology and HPV test) from the age of 30 if available (when cotest is available, controls will be made annually).

e. Annual mammogram for women between 50 and 70 years.

f. Annual PSA and digital rectal exam to all men ≥ 50 years.

g. Annual fecal occult blood to people> 40 years.

h. Annual general inspection for skin lesions suggestive of malignancy.

### Criteria for discontinuing or modifying allocated interventions {11b}

Interventions will be discontinued in case of pregnancy or revocation of the informed consent.

### Strategies to improve adherence to interventions {11c}

Adherence to the appointments will be recorded in the medical history and a new appointment arranged for the missed visits. Mobile phone messaging reminders for attendance are recommended to the participating centers after missing two visits.

### Relevant concomitant care permitted or prohibited during the trial {11d}

All concomitant interventions needed for medical care during the trial are permitted.

### Provisions for post-trial care {30}

All the included patients in the study are PLWH under medical treatment. Then, after the study, they will be cared for by their providers. The Spanish National Health Service will provide the required medical care to the study participants should they suffer harm as a result of the participation in the trial.

### Outcomes {12}

Primary outcome: diagnosis with a new NADC at stage 1 or 2, overall and for the specific cancer sites: invasive malignancies of lung, anus, liver, cervix, breast, prostate, colorectal, ovary, and invasive melanomas of skin assessed through various exams, and compared as the proportion between intervention groups at 12, 24, and 36 months.

Secondary outcomes: (1) diagnosis with a new NADC at any stage or unknown stage, overall and for the specific cancer sites: invasive malignancies of lung, anus, liver, cervix, breast, prostate, colorectal, ovary, and invasive melanomas of skin assessed through various exams, and compared as the proportion between intervention groups at 12, 24, and 36 months; (2) diagnosis with new cases of cancer diagnosed at stage 1 and 2 related to all new cases of diagnosed cancer compared as the proportion between groups at 12, 24, and 36 months; (3) unnecessary invasive procedures (with non-diagnostic results) compared as the proportion in each treatment group at 12, 24, and 36 months; (4) adverse events and severe adverse events related to the study procedures compared as the rate in each treatment group at 12, 24, and 36 months, and (5) overall mortality and mortality from cancer at 12, 24, and 36 months.

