**Enhanced screening**								
Over 40 years of age, active smokers or who would have abandoned in the last 3 years, with an accumulated index ≥ 20 pack-years and without contraindications for thoracic surgery, and without recent lung infections in the last 2 months				X		X		X
Semi-annual ultrasound and alpha-fetoprotein for all people with chronic liver disease with fibrosis ≥ F3 of any cause (including HCV infection) or any fibrosis for hepatitis B virus			X	X	X	X	X	X
Digital examination and semi-annual anal cytology MSM			X	X	X	X	X	X
Semiannual cervical cytology to all sexually active women between the ages of 21 and 64, including cotest (cervical cytology and HPV test) from the age of 30 if available (in that case, controls will be made annually)			X	X	X	X	X	X
Annual mammogram for women between 50 and 70 years				X		X		X
PSA and annual digital rectal exam to all men ≥ 50 years				X		X		X
Annual fecal occult blood to people > 40 years				X		X		X
Annual general inspection for skin lesions suggestive of malignancy				X		X		X

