### Sample size {14}

The incidence of NADCs in the previous studies SMART and ESPRIT in virologically suppressed patients with CD4> 350 and over 40 years old was approximately 0.04% during 5 years of follow-up [27]. An Italian study described an incidence of NADCs of 0.67 per 100 person-years of follow-up [28]. In the CoRIS cohort, with 31.228 person-years of follow-up, a total of 136 NADCs were diagnosed, and the incidence was 0.43 per 100 person-years of follow-up. In a study of lung cancer screening among smokers, the prevalence of lung cancer was 2.03% [29]. For the calculation of the sample size, we have estimated an incidence of cancer diagnosed at an early stage of 2% in in the intervention group and 1% in the control group. With a statistical power of 80% and a loss to follow-up percentage of 20%, it is estimated that for a unilateral contrast it would be necessary to include 2.319 subjects in the exposed group (enhanced intervention) and 2.319 in the unexposed group (standard intervention) (1:1), with a total sample of 4.638 patients.

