## Statistical methods

### Statistical methods for primary and secondary outcomes {20a}

The primary efficacy analysis will be the comparison of the proportion of cancers diagnosed at an early stage (1 and 2) in each group following the principle of intent to screen, defined as patients who accept to participate in the study and sign the informed consent, regardless of whether they are subsequently excluded due to loss of follow-up, non-adherence to study procedures, unwillingness to remain in the study, death, etc. A per protocol analysis including patients who complete the study will also be performed. A sample size of 2319 patients in each group has been calculated (expected incidence of early cancer 2% and 1% in enhanced and conventional groups, respectively; statistic power 80%; losses to follow-up 20%). Missing observations in the variables will be ignored in the analysis.

The secondary efficacy analysis will include the comparison of the incidence of cancer at any stage or unknown stage and the incidence of new cases of cancer diagnosed at stage 1 and 2 related to all new cases of cancer diagnosed.

The secondary safety analysis will compare the number of unnecessary invasive procedures, the rate of adverse events and severe adverse events, and overall mortality and mortality from cancer in both groups.

The secondary cost-utility analysis will be carried out following the recommendations of the guide for the economic evaluation of health technologies in Spain from the perspective of Spanish National Health System. The incremental cost-effectiveness ratio will be calculated, which is a measure of contrast between the increase in costs and the increase in effectiveness between the different screening alternatives compared. Statistical uncertainty will be expressed as the 95% confidence interval. Random samples of 100 patients from each group replaced 10,000 times will be projected on a graph to generate the increase in QALYs (quality-adjusted life year), the increase in costs, and the cost-effectiveness curve.

The analyses will be performed by a statistician blinded to patients’ allocation using the statistical packages SPSS® v.17 or higher, and R® 3.3 or higher. The statistical significance is set at *p* < 0.05.

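### The primary outcome covers ten outcomes at three time points with no lead comparison and no adjustment, while the sample size covers one; the wording of its denominator also needs correcting

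*Protocol article*

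**What the plan says.** Outcomes {12} gives the primary outcome as "Primary outcome: diagnosis with a new NADC at stage 1 or 2, overall and for the specific cancer sites". The sites are "invasive malignancies of lung, anus, liver, cervix, breast, prostate, colorectal, ovary, and invasive melanomas of skin assessed through various exams", which makes nine, and each result is "compared as the proportion between intervention groups at 12, 24, and 36 months". No site, time point or hierarchy is singled out.

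Statistical methods {20a} describes the primary analysis differently: "The primary efficacy analysis will be the comparison of the proportion of cancers diagnosed at an early stage (1 and 2) in each group". It mentions neither sites nor time points, and sets one threshold: "The statistical significance is set at *p* < 0.05". No division of that 5% is stated.

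Sample size {14} plans for early-stage cancer in 2% of the enhanced group and 1% of the control group, with 80% power, 20% loss and a one-sided test, giving 2,319 per group.

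Outcomes {12} lists early-stage cancers relative to all new cancers separately, as secondary outcome (2). Intervention description {11a} contains no ovarian screening in either arm, although ovary is one of the primary sites.

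**The concern.** Read as written, the primary outcome is 10 outcomes × 3 time points = 30 comparisons, each judged at 0.05, and nothing says which decides whether the trial succeeded. A result at one site or one time could be presented as a positive primary result, although only the overall comparison was sized. The setting gives such a choice room: the trial is open label, investigators at the centres adjudicate endpoints, and the steering committee has full access to interim data.

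The denominator is a second, separate problem. A more intensive programme can change how many cancers are found as well as their stage. The proportion of participants with an early cancer and the proportion of cancers that are early can therefore point in different directions. The plan should say without ambiguity which one is primary.

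**Working it through.** **Count.** Overall (1) + lung, anus, liver, cervix, breast, prostate, colorectal, ovary, melanoma (9) = 10 outcomes; × 3 time points = 30 comparisons. The 12-monthly interim efficacy looks in Interim analyses {21b} are not counted.

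**The plan's own figure.** Pooled two-proportion formula, p₁ = 0.02, p₂ = 0.01, mean p = 0.015:

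n = [z_α √(2p(1−p)) + z_β √(p₁(1−p₁) + p₂(1−p₂))]² / (p₁−p₂)²

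- One-sided: [1.645 × 0.1719 + 0.842 × 0.1718]² / 0.01² = 1,826; divided by 0.8 for loss = 2,283, against 2,319 stated (1.6% lower).
- Two-sided without loss, the same formula gives 2,319.

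Either way, one comparison has been sized.

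**Error rate with no true effect.** For independent tests, 1 − 0.95¹⁰ = 40.1% and 1 − 0.95³⁰ = 78.5%. These are upper references, because counts accumulate over time and the overall count is the sum of the sites. The correlation was therefore simulated. Inputs were 2,319 × 0.8 ≈ 1,855 evaluable per arm, Poisson counts accumulating evenly over three years, and tests at 0.05. Assumed, because the article does not give them: a 36-month risk of 1% or 2% in both arms, and site shares either equal or skewed (lung 25%, ovary 2%, the others between). This gives about 19–37 early cancers per arm, or roughly 2–4 per site with equal shares.

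| What may be claimed | Chi-square/z, two-sided | z, one-sided | Fisher exact |
|---|---|---|---|
| Overall, month 36 only | about 5% | about 5% | 3–4% |
| Overall, any of three times | 10–11% | about 10% | 7–8% |
| Any of ten, month 36 | 28–35% | 32–38% | 8–19% |
| Any of all 30 | 40–58% | 46–62% | 11–26% |

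The two-sided figures count false results in either direction. Those favouring the enhanced arm alone are about 22–34% over all 30.

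**Power for a single site.** Take the planned doubling at a site carrying a quarter or a tenth of the events (assumed shares). Power = Φ{[|p₁−p₂|√n − z_α√(2p(1−p))] / √(p₁(1−p₁)+p₂(1−p₂))}, one-sided 0.05:

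| Comparison | 2,319 per arm | 1,855 per arm (after 20% loss) |
|---|---|---|
| 0.25% vs 0.5% | Φ(−0.25) = 40% | Φ(−0.40) ≈ 35% |
| 0.1% vs 0.2% | Φ(−0.77) = 22% | Φ(−0.86) ≈ 20% |

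**Cost of keeping all ten as primary.** With Bonferroni at one time point, α = 0.05/10 = 0.005. The overall comparison alone then needs 3,450 per arm one-sided, or 4,313 with 20% loss.

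**Denominator.** Outcomes {12} (primary) and Sample size {14} count participants. The sentence in {20a} has cancers as its denominator. Read literally, it describes secondary outcome (2).

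**The case against.** The strongest reply is that the plan effectively has one primary comparison. Section {20a} speaks of a single primary efficacy analysis and repeats the 2% versus 1% sizing, and the Discussion describes the main outcome as finding more cancers at early stages, without sites or time points. On that reading the error rate is about 5% at month 36, or 10–11% over three times. This stands as the likely intention, but Outcomes {12}, where the primary outcome is defined, says otherwise and fixes no time point.

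A reader might infer that a false positive is about as likely as not. The document does not support that as a headline. It requires that any of the 30 results counts as success and that a z or chi-square test is used on a handful of events per site. The article states no such success rule and names no test, and exact tests give 11–26%.

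A reader might also see two rival primaries in the denominators, or blame the denominator for the error rate. The wording does not produce the error rate. The intent-to-screen definition and the sizing in the same paragraph of {20a} point to participants, so loose wording is the likelier explanation.

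Finally, because Table 1 marks annual tests such as "Annual general inspection for skin lesions suggestive of malignancy" at months 12, 24 and 36, one might conclude that the 12-month comparison is null by construction and that the last round is lost. Neither follows. Table 1 gives the enhanced arm liver, anal and cervical tests at month 6, and Outcomes {12} does not exclude work-ups started at the month-36 visit.

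**Conclusion.** The concern holds as a primary outcome that is badly fixed. Ten outcomes at three times are all called primary, one of them (ovary) is screened in neither arm, a single unadjusted 0.05 applies, and one comparison is sized. This concerns the definition of the outcome itself, so it is not a detail that a protocol may leave to an analysis plan.

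Its size depends on what the investigators would claim. For the overall outcome it runs from the nominal 5% to about twice that. Only if any of the 30 results may be claimed does it reach the wider range of 11–62%, and the choice of test then matters most. These ranges rest on assumed null risks and site shares. The low site-level power rests on assumed shares too, but follows the one-sided design stated in the article. The denominator wording is a separate and smaller defect that needs correcting in its own right.

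**What to change.** 1. In Outcomes {12}, name one primary: the proportion of randomised participants with a first stage 1–2 non-AIDS-defining cancer, overall, at 36 months.
2. Make the site-specific results and the 12- and 24-month results secondary, reported as estimates with 95% confidence intervals and no significance claim, or adjusted by Holm's method.
3. Reword the primary analysis in {20a} as the per-participant proportion, leaving early cancers over all cancers as secondary outcome (2).
4. As a minor addition, since Table 1 places the last annual tests at month 36, state that a cancer counts if its work-up began at or before that visit and it was confirmed within a fixed window, identical in both arms.

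This costs wording changes in the protocol, analysis plan and registry entry. The price is that no single site can carry a confirmatory claim, and the last work-ups mean a short wait. No extra participants are needed for this change.

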## Assignment of interventions: blinding

### Who will be blinded {17a}

This is an open label trial.

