### Adverse event reporting and harms {22}

Possible adverse events and other unintended effects of the trial interventions will be reported by the investigators using the electronic database notebook of the study. In addition to unnecessary interventions, expected harms of the study include the potential complications associated with the invasive interventions derived from the abnormal findings observed in the diagnostic tests. Among the most frequent, pneumothorax or bleeding occurring after biopsy of a suspected malignant lung nodule found in the CT scan; bleeding after biopsy of a lesion found during anoscopy or colonoscopy (the latter, if indicated if positive fecal occult blood test), bacteremia/sepsis after prostate biopsy performed because of abnormal PSA values, etc. All harms occurring during the study will be reported, regardless of whether they were expected or not. Severe adverse events (SAE) need to be reported to the monitor of the study in a maximum of 24 h. The monitor will notify the SAEs to the coordinators of the study. The medical monitor will also be responsible to review the reported safety data, to obtain all the useful safety information not reported by the investigators and to advice the coordinators about violations of the protocol by any center and to document it. Harms will be reported in trial publications in the “Results” section of the manuscript

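### The between-arm harm rate is limited to procedure-related events in one section and unrestricted in others, and in this open-label design the restriction can sort the same complication differently by arm

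*Protocol article*

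**What the plan says.** The protocol describes the adverse event comparison in four places.

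- Outcomes {12}, fourth secondary outcome: "adverse events and severe adverse events related to the study procedures compared as the rate in each treatment group". The comparison is made yearly up to month 36.
- Hypothesis and objectives {7}: "to analyze safety of the program: adverse events and unnecessary interventions". No relatedness restriction.
- Statistical methods {20a}: the safety analysis compares "the rate of adverse events and severe adverse events, and overall mortality and mortality from cancer in both groups". No relatedness restriction.
- Adverse event reporting and harms {22}: it opens with "Possible adverse events and other unintended effects of the trial interventions will be reported by the investigators using the electronic database notebook of the study", and later adds "All harms occurring during the study will be reported, regardless of whether they were expected or not".

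Four other statements bear on how the restriction would work. Under {17a}, "This is an open label trial". Under {5d}, site investigators adjudicate endpoints, and the data monitoring committee may be consulted on unclear cases that need an oncologist. Under {11d}, any concomitant intervention needed for care is allowed. The abstract says that the "Conventional intervention group will follow the standard of care screening in the participating centers", in line with European guideline recommendations, and {11a} then lists those procedures.

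**The concern.** The trial asks whether the benefits of enhanced screening outweigh its harms. Outcome (4) is the only between-arm measure of non-fatal complications. Outcome (3) counts non-diagnostic invasive procedures, not what happens after them. Outcome (5) is mortality, and the Discussion concedes that the sample is too small to detect mortality differences.

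A comparison limited to events attributed to study procedures is fair only if that phrase means the same in both arms. Here one arm receives an expanded programme and the other follows usual practice. The article does not say whether work-up that began in ordinary care counts as a study procedure in the conventional arm. If it does not, part of that arm's harm is left out of the rate because of allocation and not because of what happened to the patient.

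**Working it through.** The plan gives no adverse event rate, harm margin or power for safety, so there is no stated figure to reproduce. The check is a comparison of the text, followed by an illustration on assumed inputs.

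**1. Which events are compared?** {12}(4) says related events only. {7} and {20a} name adverse events without that limit. {22} first speaks of effects of the trial interventions, then of all harms. Being expected or unexpected, which {22} mentions, is a different matter from being related or unrelated. The event set is therefore not settled.

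**2. Does the related-only filter depend on the arm?** Procedures listed in {11a}:

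- Both arms: liver, anus, cervix, breast, prostate, colorectum (6 of the 8 enhanced items).
- Enhanced arm only: low-dose CT and skin inspection (2 of 8).
- Shared items also differ in reach. Fecal occult blood testing is for people over 40 in the enhanced arm and for ages 50 to 75 in the conventional arm, so between 40 and 50 it is listed for the enhanced arm only.

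Take one event that {22} itself names, a pneumothorax after biopsy of a suspicious lung nodule.

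- Enhanced arm, nodule found on protocol CT: the biopsy follows from a study procedure, and the event is inside {12}(4).
- Conventional arm, nodule found on imaging in ordinary care, as {11d} allows: no listed procedure led to it. The event is reported under {22} but falls outside {12}(4) as written.

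The complication is the same and its classification differs.

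**3. What could this do to the comparison?** All rates and labelling shares here are assumptions. Only n = 2319 per arm comes from the protocol. The rate is treated as the proportion of patients with an event, without losses.

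Observed rate = true rate × share labelled related. With equal true rates, the observed ratio is the ratio of the shares:

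- 90% enhanced, 70% conventional: 0.9/0.7 = 1.29
- 90% enhanced, 50% conventional: 0.9/0.5 = 1.80

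Chance of a significant result (two-sided 0.05), with p̄ the mean of p1 and p0:

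Φ{ [ |p1 − p0| − 1.96 √(2p̄(1 − p̄)/n) ] / √([p1(1 − p1) + p0(1 − p0)]/n) }

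For true harm of 5% and shares of 90% and 70%: p1 = 0.05 × 0.9 = 0.045, p0 = 0.05 × 0.7 = 0.035, p̄ = 0.040. The two standard errors are 0.005755 and 0.005753. Then (0.010 − 1.96 × 0.005755)/0.005753 = −0.22, and Φ(−0.22) = 0.41.

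| True harm, both arms | Shares 90% / 70% | Shares 90% / 50% |
|---|---|---|
| 2% | 19% | 64% |
| 5% | 41% | 96% |
| 10% | 71% | about 100% |

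Each entry is the chance of a significant apparent excess in the enhanced arm when the true rates are equal.

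**4. Is the direction known?** No. Step 3 assumes that control events are labelled less often, which inflates the ratio. A narrow reading of study procedures can also work the other way. Suppose 30 diagnostic complications in the enhanced arm and 15 in control, plus 20 extra complications of cancer treatment in the enhanced arm that are not counted. Then 50/15 = 3.3 would be reported as 30/15 = 2.0. These counts are assumed too, and whether treatment complications belong in the rate is itself a design choice.

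**The case against.** The strongest reply is that {20a} is shorthand. It also drops the non-diagnostic qualifier from outcome (3) and the time points for the safety outcomes, so "the rate of adverse events and severe adverse events" may simply mean outcome (4). That is a fair reading. A reader might infer that {20a} counts all adverse events and so flatly contradicts {12}. It does not use the word all, and ambiguity is as far as the text goes.

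Second, the conventional arm is not free of procedures. Sepsis after a biopsy prompted by a control-arm PSA test might look like an event that would be left out, but PSA is an optional listed item for that arm in {11a} and appears in Table 1, and {22} names this complication without limiting it to one arm. This narrows the asymmetry. It does not reach procedures listed for the enhanced arm only, or work-up begun in ordinary care.

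Third, a reader might infer that harms are collected unequally or that the bias could not be undone. The documents do not support that. {22} asks for all harms with no difference by arm, and makes the medical monitor responsible for obtaining safety information that investigators have not reported. If that is followed, an unrestricted comparison remains possible. What stands is the classification problem in the outcome as defined.

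Fourth, no section says who judges relatedness. That it would be an investigator who knows the allocation is an inference from {17a}, {5d} and {22}, and the full protocol may name the assessor and criteria. The pneumothorax example does not depend on this, because it follows from what counts as a study procedure.

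Finally, treatment harms are partly covered elsewhere. Mortality is compared without a relatedness limit, and {20b} varies operative mortality and treatment costs in sensitivity analyses. Adding treatment toxicity to the main harm rate would be a preference, not a correction.

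**Conclusion.** The point holds as an ambiguity together with an arm-dependent filter. The safety outcome in {12} is restricted to related events, while {7} and {20a} are not. With low-dose CT and skin inspection listed for one arm only, open-label conduct, site adjudication and ordinary-care work-up permitted, the restricted rate can classify the same complication differently by arm and so bias the harm comparison.

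Size and net direction are unknown. Ratios of 1.29 to 1.80 under equal true harm rest on assumed labelling shares and show only that the bias is possible. The documents do not show that it occurs, that data would be lost, or that sites would apply the filter in any particular way.

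**What to change.** State one between-arm safety outcome in {12}(4) and repeat it in {20a}: adverse events and severe adverse events following any screening test or diagnostic procedure for suspected cancer at a listed site, in both arms, whatever prompted the procedure and regardless of attributed relatedness, over all randomised patients.

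Keep investigator-attributed relatedness as a descriptive column. Report complications of cancer treatment separately by arm as a descriptive supplement.

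The cost is wording in two sections, one instruction to sites that ordinary-care work-up in the conventional arm is included, and slightly more event entry in that arm. {22} already requires all harms to be reported, so no new kind of data collection is needed.
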